##### Glycemia

The day before the race, the investigators placed a continuous interstitial glucose sensor (FreeStyle Libre Pro, Abbott) on the back of participants’ arms. This sensor was used in masked mode; hence, the runners did not have live access to their blood glucose values, so as not to interfere with their usual running strategies. The sensor is self-calibrating and does not need to be manipulated once fitted. Blood glucose levels were estimated from interstitial glucose levels measured at 15-minute intervals from the time the sensor was fitted until it was removed 9 days after the race.

In addition, plasma glucose levels were analyzed from venous blood samples collected on the morning before the race, at the end of each loop, at the end of the race, and 24 hours after the race.

##### Sleep Exploration

A sleep questionnaire, adapted from the existing Spiegel, Epworth, and Vis-Morgen questionnaires, was administered to all participants before, during (if a nap was required), and after the race.

On the night before the race and the 7 nights after the race, the participants were equipped with the Hexoskin Pro Waistcoat, measuring sleep indirectly by actimetry.

Sleep was also recorded by electroencephalogram measurements using a Somfit (Compumedics Limited) for naps during the race and in the 7 nights following the race for a subgroup.

On the day before the race, the day of the start of the race, at the end of each loop, and at the end of the race or retirement, participants were asked to complete the Karolinska Subjective Sleepiness Scale.

#### Biomechanical Exploration

##### Elastic and Architectural Properties of the Gastrocnemius-Achilles Tendon Complex

Ultrasound examination was performed using a linear array transducer (EPIQ Elite with eL18-4 transducer ElastQ Imaging shear wave elastography, Philips Medical Systems). All participants were examined in the prone position, with the knee in the extended position and the ankle fixed in a neutral position. Both legs were assessed. The cross-sectional area of the Achilles tendon (in mm^2^) was measured at the level between the malleoli [79]. Longitudinal panoramic sonographic images of the medial gastrocnemius muscle were obtained. Pennation angle and fascicle length were measured at the middle and distal parts of the muscle [80]. The elastic properties of the medial gastrocnemius muscle were measured in the longitudinal view at 30% of the muscle length using Young modulus values (in kPa) determined by shear wave ultrasound elastography [81]. The region of interest circle was placed in the muscle belly, and median elasticity, maximum elasticity, and average elasticity were collected. Measurements were performed before the race and repeated at the end of the second lap, the fourth lap, at the end or at retirement, and 6 hours after the race.

##### Running Kinetics and Kinematics

The data were collected on the day before the Trail Scientifique Clécy (10 minutes of warm-up before data collection for a few seconds for the kinematics); during the race; at the end of each loop; and 30 m before the end of a lap on a flat, paved, and covered portion.

The kinematics of the race were evaluated using a high-definition video camera and an Optojump system (Microgate) at the end of each loop. The characterization of foot strike patterns (rear foot, midfoot, and forefoot) using a video camera is a valid and accurate method of assessment [82-84]. The foot strike angle at the initial contact was also measured using a high-speed, high-definition camera at 240 frames per second. Step rate, step length, and ground and fly contact time were measured using an Optojump system comprising fixed sensors of 15 m × 1.5 m, which were positioned in an 18 m × 3 m tent on a level section. This instrument has been validated against an instrumented treadmill [85].

RunScribe sensors were used continuously throughout the run to measure the kinematic parameters of the stride. The variables of interest were the foot strike pattern, power, flight time, flight ratio, step rate, and ground contact time, which were previously found to be valid and reliable [86].

The loops were broken down into sections (ascent, descent, and flat) to isolate the variables and analyze the intermediate race times.

##### Shoes

The day before the race, information was collected on the trail shoes used by the participants (brand, model, size, weight, sole thickness and drop, torsional and longitudinal flexibility, motion control technologies, and the Minimalist Index [87]). A questionnaire was also administered to define their needs, expectations, and preferences regarding the footwear used.

##### Foot Measurement

Both feet were scanned using a photogrammetric 3D scanner (FeetBox3D, Corpus-e). A 3D model of the feet was reconstructed to observe the structural changes induced by the race (swelling).

This measurement was taken before the race and repeated at the end of each lap and at the end of the race or retirement.

#### Cognitive, Psychological, and Sociological Exploration

##### Vestibular System: Testing Sensory Organization and Measuring Spatial Orientation

We assessed verticality perception to evaluate the visuovestibular sensory preference with subjective vertical visual, dynamic subjective vertical visual, and the Rode and Frame test 4 hours before the race, at loops 1 and 3, at the end loop 6, and 24 hours after the race.

We measured the spatial strategy according to the egocentric (striatal network) versus allocentric (hippocampal network) response through the reverse T maze previously performed in rodents [88] and in healthy participants [49] before the race, at the end of loop 6, and at 24 hours after the race.

All tests were performed using a virtual reality headset setup (VRMaze [89]).

##### Postural Control

Postural control was measured 2 times for 50 seconds (open and closed eye conditions) on K-Force Plates (K-Invent).

This measurement was repeated 24 hours and 3 hours before the race, at loops 1 and 3, at the end of loop 6, and 24 hours after the race. Anteroposterior and lateral sway and stability scores were analyzed.

##### Cognitive Tests

On the day before the race, the morning of the race, at the end of each loop, and then at the end or at retirement, the runners were asked to assess a simple 5-minute serial response time test [90]. The number of mistakes termed *errors of omission* (eg, lapses of attention, historically defined as response time ≥500 milliseconds) plus *errors of commission* (eg, responses without a stimulus, false starts, or response time <100 milliseconds) are the primary outcome measures. The mean response times were also calculated. A measure of perceived sleepiness using the Karolinska Sleepiness Scale completed the objective assessment.

##### Psychomotivational Test

On the morning of the race, at the end of each loop, at the finish line, and 24 hours after the race, participants completed a motivational test.

The methodology comprised asking participants to perform 2 tests on a computer, each lasting approximately 3 minutes. A long version of these tests was described by Schmidt et al [91]. One was for physical effort, and the other was for mental effort. The short version was implemented during the Reunion ultratrail (Grand Raid).

In each test, participants were asked to try to win as much money as possible. The money was not real, as in a video game; however, the amount won is used to rank participants. Each trial had a coin or note (10c or 0.11c, €1 or US $1.06, or €10 or US $10.58) that one can win if they do their best. The maximum was specific to each participant and was measured during the prerace visit, which allowed instructions to be given.

Each test comprised 9 trials, 3 per incentive level, where the participant must either squeeze the handle as hard as possible or solve as many numerical comparisons as possible in a limited time. At the end of each trial, the participant was told his or her performance and the amount of money earned, calculated as the fraction of the incentive corresponding to the fraction of the maximum effort achieved. The maximum effort corresponds to the maximum muscular contraction produced during the calibration visit and the minimum time taken to complete 10 numerical comparisons.

##### Sociological Questionnaire

Before the race, the participants had to fill in a sociological questionnaire on their ability to be attentive to themselves, others, and the world using various indicators.

#### Environmental Exploration

To measure the air quality, we installed 2 sensors (Air Quality Transmitter AQT530, Vaisala) along the course of the trail of Clécy at a height of 1.70 m from the ground. The sensors were placed at 2 locations along the course. The first sensor was located at the center of the Pleine Nature Lionel Terray at the start of the race. This point was also the passage of each 26 km loop and the arrival of the race. This was the point of the course with the lowest altitude (50 m). The second sensor was located at the aid station at the 14th kilometer of the course, which was the point of the course with the highest altitude (254 m). The frequency of the measurement of the sensors was 1 measurement every 10 minutes.

These sensors measured nitrogen dioxide, nitrogen monoxide, carbon monoxide, ozone, and fine particles (particulate matter [PM]) with diameters <1 µm (PM1), <2.5 µm (PM2.5), and <10 µm (PM10). Environmental parameters such as temperature, humidity, and atmospheric pressure were also recorded.

#### Other Measures

Crosscall Core T4 tablets (France) with Quicktape Survey software (Canada) were used to merge the questionnaires of each scientific team.

#### Order of Tasks

To reduce the impact of one measure on another for the prerace measurements, the order of passage of the tasks was imposed. Therefore, no randomization was performed.

Figure 1 shows the sequence of the scientific part.

**Figure 1 figure1:**
[figure not shown]
Organization of scientific measurements.

### Statistical Analysis

Data related to the primary and secondary objectives will be evaluated at the end of the study. For each studied parameter, the normality of the distribution will be examined using the Shapiro-Wilk test. Continuous quantitative variables will be expressed as mean (SD), discontinuous variables as median and IQR, and qualitative variables as percentages. The comparison of the values of the primary end point between the baseline and the end of the study will be performed using statistical tests for the paired series. In addition, to take into account repeated measures over time, we will analyze the primary end point as a function of time using appropriate mixed models for repeated data. Using the same statistical tests as for the primary end point, we will analyze the secondary end points. The threshold for statistical significance will be defined as *P*˂.05. Depending on the scientific team, we will use MedCalc Statistical Software (version 13.2.0) and JASP (version 0.16.1.0) or RStudio (version 1.2) to perform the statistical analyses.

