### Objective

The objective of this protocol was to study in situ the kinetics of the factors determining performance in an ultraendurance trail-running event. This main objective is broken down into several scientific disciplines, each of which includes subobjectives (Textbox 1).

Objectives based on scientific disciplines.

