##### Blood Biology

On the morning of the race, at the end of each loop, at the end of the race, and 24 hours after the race, venipuncture was performed on participants in a sitting position. Blood samples (2 mL) were collected from the forearm in heparin and citrate tubes. The samples were centrifuged and aliquoted for further analysis. Coagulant-free serum, serum EDTA, and heparinized vacutainers allowed us to obtain serum and plasma for the following further analyses:

Plasma levels of interleukin (IL)-1, IL-6, tumor necrosis factor (TNF)-α, protein S100, neuron-specific enolase, C-reactive protein (proinflammatory markers), and IL-4, IL-10, and IL-13 (anti-inflammatory markers)The parameters studied related to sepsis will be granzyme B, heat shock protein 70, IL-1α, IL-8, macrophage inflammatory protein 1 α, macrophage inflammatory protein 1 β, and matrix metalloproteinase-8The studied parameters related to metabolism will be ghrelin, gastric inhibitory polypeptide, glucagon-like peptide-1, glucagon, insulin, insulin leptin plasminogen activator inhibitor-1 (total), resistin, visfatin, C-peptide, cortisol, pancreatic polypeptide, insulin, and peptide YYThe parameters studied related to inflammation will be soluble CD30, soluble epidermal growth factor receptor, soluble glycoprotein 130, soluble IL (sIL)-1 receptor type I, sIL-1 receptor type II, sIL-2 receptor type α, sIL-4 receptor, sIL-6 receptor, advanced glycosylation end product-specific receptor, soluble TNF receptor I, soluble TNF receptor II, soluble vascular endothelial growth factor (sVEGF) receptor 1, sVEGF receptor 2, and sVEGF receptor 3The parameters studied in relation to renal function will be blood count and blood ionogram with calcium, phosphorus, magnesium, urea, creatinine, neutrophil gelatinase-associated lipocalin, kidney injury molecule 1, plasma, and urine lipocalin

Venous blood gas analysis was immediately performed using the Stat Profile Prime (Nova Biomedical) medical device, allowing hemoglobin measurement and hematocrit calculation.

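### One P<.05 threshold for all end points, with a primary end point that is never identified, leaves about 50 blood analytes and the other secondary variables without stated error control

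*Protocol article*

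**What the plan says.** The Statistical Analysis section gives two analyses for the primary end point. The first is a paired test, for which the plan names this contrast: "The comparison of the values of the primary end point between the baseline and the end of the study". The second is longitudinal: "we will analyze the primary end point as a function of time using appropriate mixed models for repeated data". The section then extends this to everything else: "Using the same statistical tests as for the primary end point, we will analyze the secondary end points". The next sentence sets one threshold for all of it: "The threshold for statistical significance will be defined as" P<.05. No adjustment, testing order or exploratory label is stated.

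The article does not say which variable the primary end point is. On the main objective, the Objective section says only this: "This main objective is broken down into several scientific disciplines, each of which includes subobjectives". Textbox 1 lists 15 subobjectives (7 physiological, 3 biomechanical, 4 psychocognitive and sociological, 1 environmental) and ranks none of them. The word primary is attached to a measured variable in one place only, the Cognitive Tests section, where omission and commission errors "are the primary outcome measures". That describes the response-time test, not the study.

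Blood Biology lists five groups of markers, sampled "On the morning of the race, at the end of each loop, at the end of the race, and 24 hours after the race".

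**The concern.** A primary/secondary hierarchy protects against chance findings only if the reader knows which variable is primary. Here the hierarchy is invoked but left empty, and every variable meets the same .05 threshold. Nothing in the article then separates a confirmatory result from one picked out of a long list.

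This matters because the study's general hypothesis, in the abstract, is framed as significant alteration of many kinds of parameter. Statistical significance is therefore the label by which results will be read. Some questions may well have true nulls. The Discussion expects a plateau in the last third of the race, so many late-lap differences should be absent. Other aims, such as the association of air quality with physiology or a circadian effect on the kinetics, may also show nothing. A marker that is significant by chance would look the same as a real change.

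**Working it through.** **The plan's own figure.** The article gives no error rate and no number of tests, so there is none to reproduce on this point. Its one design figure with stated inputs is the expected number of finishers: 55 × (1 − 0.25) = 41.25, inside the stated 40 to 45. Results reports 41 finishers and 14 non-finishers, which bears on the fix.

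**Step 1: count the analytes (Blood Biology).**

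| Group | Distinct analytes |
|---|---|
| Pro- and anti-inflammatory | 9 |
| Sepsis | 7 |
| Metabolism (insulin counted once; leptin and plasminogen activator inhibitor-1 counted separately) | 13 |
| Soluble receptors | 14 |
| Renal and electrolytes, single analytes only | 7 |
| **Total** | **50** |

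Merging IL-1 with IL-1α would give 49. The blood count, other ionogram items, urine lipocalin, hemoglobin, hematocrit and plasma glucose are not counted and would take the total back above 50.

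**Step 2: one test per analyte at .05, all 50 nulls true.**

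- Expected false positives: 50 × 0.05 = 2.5. This does not depend on correlation, but it falls in proportion as fewer nulls are true.
- Chance of at least one, tests independent: 1 − 0.95^50 = 0.923.

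**Step 3: allow for correlation.** Markers from the same samples are probably correlated. Assume two-sided tests (the article does not state sidedness) and normal test statistics with common correlation ρ. With c = 1.96, the chance of at least one false positive is

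1 − ∫ [Φ((c − √ρ·x)/√(1−ρ)) − Φ((−c − √ρ·x)/√(1−ρ))]^50 φ(x) dx.

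| ρ | Chance of at least one (50 true nulls) |
|---|---|
| 0 | 0.923 |
| 0.1 | 0.906 |
| 0.3 | 0.805 |
| 0.5 | 0.622 |
| 0.7 | 0.404 |

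**Step 4: allow for real effects.** With m true nulls and independent tests, the chance is 1 − 0.95^m and the expected count is 0.05 × m.

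| m | Chance of at least one | Expected false positives |
|---|---|---|
| 50 | 0.923 | 2.5 |
| 25 | 0.723 | 1.25 |
| 10 | 0.401 | 0.5 |
| 5 | 0.226 | 0.25 |

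**Step 5: two analyses per end point.** The plan specifies a paired test and a mixed model for each variable. If these were 100 independent null tests, the chance would be 1 − 0.95^100 = 0.994, with 100 × 0.05 = 5.0 false positives expected. The two analyses of one analyte share data, so 0.994 is an upper limit.

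**The case against.** The strongest objection is that *unadjusted* is read from silence. This is a condensed article; the full protocol and any analysis plan are not shown, and multiplicity procedures are commonly left to them. That stands as a limit: nobody can say from this text that no adjustment will be made. It does not remove the point. The article itself fixes the threshold, extends the same tests to all secondary end points and relies on a primary end point that its own text never identifies.

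The second objection is that the study expects real change. The Discussion hypothesizes degradation of all the functions studied, so a scenario in which no analyte changes is not the investigators' own expectation. This also stands. It is why 2.5 and 92% are upper figures for one test per analyte.

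Three stronger readings are tempting but not supported.

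- *False positives are almost certain.* Even 92% needs 50 true nulls and independence; Steps 3 and 4 show how far it falls otherwise.
- *Seven comparisons with baseline per analyte, hence 50 × 7 = 350 tests and 17.5 false positives.* The sampling schedule would allow this, but the plan specifies one baseline-to-end comparison and a model over time, not a contrast at each draw.
- *Every team's paper will contain chance findings.* Only the choice of software is tied to the team, and disciplines with few variables carry much less risk. Three independent null tests give 1 − 0.95^3 = 0.143.

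**Conclusion.** The point holds in a limited form. The article applies one P<.05 rule and the same tests to primary and secondary end points, states no adjustment, and does not identify the study-level primary end point. The hierarchy it invokes therefore controls no error.

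For about 50 blood analytes tested once each, the consequence is up to 2.5 expected false positives and up to a 92% chance of at least one. The first figure assumes that no analyte truly changes; the second also assumes independence. The chance is about 62% with all 50 nulls true and a common correlation of 0.5, and about 40% with 10 independent true nulls. The true share of nulls and the correlation are unknown, so these figures show a range and do not predict the outcome. An adjustment in an unseen document would answer the multiplicity part, but the article's missing primary end point would still need correcting.

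**What to change.** 1. Name the primary end point that the Statistical Analysis section tests, or label the whole study exploratory. Naming one primary per Textbox 1 subobjective would not do by itself: 15 unadjusted primaries give 1 − 0.95^15 = 0.537 if all are null and independent.
2. For all other variables, replace the flat P<.05 rule with Benjamini-Hochberg control at a 5% false discovery rate within each discipline's family, for example all blood analytes together. Apply it to one global test of time per variable. Its standard guarantee assumes independent or positively dependent tests.
3. Examine lap-level contrasts only where the global test passes.
4. For baseline-to-end contrasts, use the end-of-race or retirement measurement where one was taken. The Race section requires postrace testing of runners who drop out; a contrast tied to lap 6 would discard the end values of the 14 non-finishers. Measures taken only before the race, such as the sociological and shoe questionnaires, have no such contrast and need their own stated analysis.
5. Report adjusted P values with confidence intervals.

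The cost is wording agreed across the teams; no new data are needed. Some markers near .05 will no longer be called significant. The loss is small where effects are common: if 40 of 50 analytes are clearly significant, the 41st is compared with 41/50 × 0.05 = 0.041. It is larger where effects are sparse: a single outstanding analyte is compared with 0.05/50 = 0.001.

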### Ethics Approval

The launch of the study was authorized on October 26, 2021, under trial number 21-0166 after a favorable opinion from the Comité de Protection des Personnes Ouest III (21.09.61/SIRIPH 2G 21.01586.000009).

Time (all runners n=54), mean (SD)	3.0119 (0.3344)	3.5217 (0.4306)	3.9736 (0.6708)	4.2397 (0.6608)	4.4114 (0.9072)	4.6444 (0.9625)
Time for finishers (n=41), mean (SD)	2.9633 (0.35)	3.4528 (0.4197)	3.8631 (0.6214)	4.1261 (0.5825)	4.3144 (0.8425)	4.6444 (0.9625)
Time for did not finish, mean (SD)	3.1536 (0.2419)	3.7236 (0.4117)	4.3511 (0.7231)	4.7578 (0.78)	5.7367 (0.8175)	N/A^a^

^a^N/A: not applicable (there are no more runners in this category on lap 6 as they did not finish the race).

### Undesirable Effects

No runner had to interrupt the race because of an undesirable effect of the protocol.

We noted a few lipothymia cases, which were not serious, during certain scientific tests, particularly those requiring prolonged standing.

We did not note any muscle damage related to the tests.

The venipunctures generated ecchymosis because of the difficulty of puncturing but also extravasation secondary to the rapid resumption of the race (strong and lasting compression not being possible).

Anecdotally, 8 punctures, 6 of which were during the race, were a major constraint.

## Discussion

### Principal Findings

The Trail Scientifique de Clécy allowed, for the first time, an integrative and multidisciplinary approach to better understand the performance of ultramarathons. The hypotheses based on the observations of the studies conducted in trail running go in the direction of degradation of many functions in the first one-third of the race before reaching a plateau in the last one-third of the race, suggesting that the differences in certain parameters of tiredness are no longer significant between the arrival of 100 miles or 200 miles in a mountain [3,4,20,41,42,48,92-94].

Thus, our initial hypothesis was that there is a significant degradation of all the studied functions under the effect of race-induced fatigue from the first one-third of the race before reaching a plateau on the third one-third. We assume that a difference or difference in the kinetics of the studied functions can lead to failure and abandonment.

Owing to its duration, a mountain ultramarathon induces night and day phases, which can induce a circadian effect on the fluctuation of physiological and cognitive functions. Our team is interested in verifying whether there is a circadian effect on the kinetics of the functions studied during the Trail Scientifique de Clécy, according to the running time and the time of day.

Our study population is representative of the real population of a classic ultratrail race. Our average age (45, SD 13.6 years) is in line with the recent observations, who reported that the average age of the different races of the Ultra Trail du Mont Blanc (Courmayeur Champex Chamonix and Orcières Champex Chamonix) from 2014 to 2018 for the 40 to 49 age group is the most represented [95]. Concerning the distribution of men and women, 21.8% of women against 9.8% of women are on the starting line for the Ultra Trail du Mont Blanc 2021 [95].

The downtime imposed to meet the requirements of the scientific protocol did not exceed 20% of the total time. These data allow us to justify that our scientific race model is closer to reality because of the reduced duration of the stopping time for scientific tasks compared with the duration of the race and voluntary stops.

